## Abstract

**Background:**

Adolescent-onset depression often results in a chronic and recurrent course, and is associated with worse outcomes relative to adult-onset depression. Targeting habitual depressive rumination, a specific known risk factor for relapse, may improve clinical outcomes for adolescents who have experienced a depressive episode. Randomized controlled trials (RCTs) thus far have demonstrated that rumination-focused cognitive behavioral therapy (RFCBT) reduces depressive symptoms and relapse rates in patients with residual depression and adolescents and young adults with elevated rumination. This was also observed in a pilot RCT of adolescents at risk for depressive relapse. Rumination can be measured at the self-report, behavioral, and neural levels- using patterns of connectivity between the Default Mode Network (DMN) and Cognitive Control Network (CCN). Disrupted connectivity is a putative important mechanism for understanding reduced rumination via RFCBT. A feasibility trial in adolescents found that reductions in connectivity between DMN and CCN regions following RFCBT were correlated with change in rumination and depressive symptoms.

**Method:**

This is a phase III two-arm, two-stage, RCT of depression prevention. The trial tests whether RFCBT reduces identified risk factors for depressive relapse (rumination, patterns of neural connectivity, and depressive symptoms) in adolescents with partially or fully remitted depression and elevated rumination. In the first stage, RFCBT is compared to treatment as usual within the community. In the second stage, the comparator condition is relaxation therapy. Primary outcomes will be (a) reductions in depressive rumination, assessed using the Rumination Response Scale, and (b) reductions in resting state functional magnetic resonance imaging connectivity of DMN (posterior cingulate cortex) to CCN (inferior frontal gyrus), at 16 weeks post-randomization. Secondary outcomes include change in symptoms of depression following treatment, recurrence of depression over 12 months post-intervention period, and whether engagement with therapy homework (as a dose measure) is related to changes in the primary outcomes.

**Discussion:**

RFCBT will be evaluated as a putative preventive therapy to reduce the risk of depressive relapse in adolescents, and influence the identified self-report, behavioral, and neural mechanisms of change. Understanding mechanisms that underlie change in rumination is necessary to improve and further disseminate preventive interventions.

**Trial registration:**

ClinicalTrials.gov Identifier: NCT03859297, registered 01 March 2019.

## Background

Depression is a leading cause of disability, affecting more than 264 million people worldwide [1, 2]. The prevalence of depression has increased by nearly 20% in the last decade. Notably, the greatest increase in incidence for depression is during adolescence and early adulthood. In addition, 25% of individuals experience their first depressive episode before the age of 19 [1–4]. Despite the availability of well-established treatment options (e.g., cognitive behavioral therapy, CBT; antidepressant medications), significant challenges in the prevention and treatment of depression remain. There is considerable evidence indicating that depression is sub-optimally treated by existing psychosocial and pharmaceutical interventions (e.g., [5–7]), with a 40-60% remission rate. Of those in remission, 30-50% experience residual symptoms at the end of treatment [8–10], with high rates of relapse. A recent meta-analysis of adults reported that 29% of patients experienced relapse within 1 year and 56% experienced a recurrence within 2 years [11], with similar statistics in adolescents [12], emphasizing that for many, depression has a chronic recurrent course.

Adolescence is a key developmental window in which to intervene with individuals who are vulnerable to depressive episodes [13], as depressive illness has cumulative educational, psychosocial, occupational, and economic burden. Moreover, adolescent-onset depression typically follows a chronic, recurrent course, and is associated with more negative outcomes relative to adult-onset depression [14–21]. Evidence also exists that the recurrent form of depression tends to worsen as individuals transition into adulthood, with more severe and longer episodes [22]. However, current gold-standard treatments do not successfully treat a substantial number of adolescents (30-60%) and are not effective in reducing risk of relapse [12]. As a consequence, there is a rapidly expanding literature investigating interventions to reduce depression in adolescence and emerging adulthood, and to prevent relapse and recurrence in this age group [23]. Finally, adolescence is a period in which healthy habit development might achieve sustained benefits.

One proposed means to reduce depression recurrence in young people is to use preventive interventions that target specific proximal risk factors that have an established role in the onset, maintenance, and recurrence of depression. Meta-analyses have reported that whereas universal preventive interventions (aimed at whole populations) achieve only small-to-non significant effect sizes [24], targeted interventions (aimed at individuals presenting with subclinical symptoms and/or established risk factors) have larger reductions in hazard ratios, and these effects are sustained over a longer period [25, 26]. Within the framework of these proximal risk factors, there is an increased appreciation that the mechanisms underlying increased risk for psychopathology may be dimensional in nature, and may even be transdiagnostic [27–29]. For example, the Research Domain Criteria (RDoC) framework by the National Institute of Mental Health (NIMH) proposes dimensional risks for illness can exist along a continuum and may not be specific to a given disorder [27, 28]. Novel interventions should therefore seek to alter such mechanisms in order to effectively target the emergence and maintenance of mental health difficulties such as depression. Building on this framework, prevention mechanism trials [30] seek to establish whether interventions can reduce specific risk factors for psychopathology or increase established resilience factors.

Rumination is a known proximal risk factor implicated in the onset, maintenance and relapse of depression, and has been identified as a malleable target for intervention [31, 32]. Prospective longitudinal research has demonstrated that degree of ruminative habit (i.e., the frequency, intensity and automaticity of ruminative thought in response to negative affect) predicts (a) onset and duration of major depressive episodes [33, 34]; (b) depressive symptoms, after controlling for baseline depression and anxiety, across a range of follow-up periods [35, 36]; and (c) slower response to CBT and antidepressant treatment, as well as reduced likelihood of recovery following treatment [37, 38]. Degree of ruminative habit also mediates the effects of other identified risk factors on depressive onset [39]. Importantly, rumination is a sensitive, relevant risk factor for adolescent depression and prospectively predicts fluctuations in depressive symptoms over time in this age group [33, 40, 41]. Developmental studies indicate that the ruminative response style emerges and stabilizes during the transition from childhood to adolescence, consolidating into an emotionally pernicious habit that is strongly predictive of psychopathology in adolescence (see [42] for recent review). The emergence of rumination coincides with a period of rapid cognitive and neural development, during which continued, significant structural and functional changes are observed within the cognitive control network (CCN) and increasing connectivity within the default mode network (DMN) [42–48]. It has been suggested that increasing coherence within these brain networks may be important to understanding the emergence of rumination as a habitual response style during this developmental window [42].

Rumination has been related to abnormal functioning of key nodes and networks of the brain. From resting state and mood induction studies, evidence is present that rumination is associated with elevated activation and connectivity between DMN nodes (e.g., [49]), increased connectivity between CCN and DMN, and reduced connectivity within CCN. The DMN is thought to support self-referential processing, passive waiting, and attention to the internal environment. Both resting state-functional MRI (rs-fMRI) and task-based approaches have been employed to study the neural correlates of rumination among adults, and to a lesser extent, adolescents with depression [45, 49–58]. The temporal correlation of blood-oxygen level dependent (BOLD) activation, and perhaps synchronization and engagement, of specified nodes of the brain are reflected in rs-fMRI measures. Self-reported rumination is related to activation in regions of the DMN during task-based studies, including the dorsomedial prefrontal cortex (dmPFC), posterior cingulate cortex (PCC), and also visual and somatosensory areas. Alternatively, activation in the superior frontal gyrus in the CCN has been found during rumination induction tasks [48, 50, 52]. The CCN is a distinct network of distributed neural nodes that broadly supports integrative executive functions such as inhibitory control, working memory, and sustained complex attention [59]. One function of inhibitory control is its ability to modulate negative affective processes, including rumination [46, 60, 61]. Consistent with a CCN disruption hypothesis of elevated rumination, rs-fMRI studies have reported that disrupted/elevated DMN-CCN connectivity (and decreased within CCN connectivity) is associated with increased rumination and decreased inhibitory control [46, 61, 62]. Moreover, behavioral disruption is evident in the context of induced rumination in the laboratory, with more errors and greater interference (slower response times) observed during a concurrent attentional task [48, 63]. As such, the maladaptive effects of rumination can be observed at both the clinical level, in elevated risk for depression, and at the neural and behavioral level, including impaired performance on cognitive tasks and altered functioning of key brain networks.

A recent systematic review examined whether treatments for depression that specifically target rumination produce better outcomes than more generic treatments that do not target rumination [64]. Results showed that treatments specifically targeting rumination had significantly larger effect sizes in reducing rumination than other treatments. These effects on rumination post-treatment were significantly associated with reductions in depression severity only in variants of cognitive-behavioral therapy specifically designed to target rumination such as rumination-focused CBT (RFCBT) [64]. RFCBT differentiates between functional and dysfunctional styles of repetitive thinking; the more adaptive thinking style is conceptualized as being concrete and specific, whereas the unhelpful thinking style is abstract and evaluative, consistent with the phenomenology of depressive rumination. RFCBT conceptualizes ruminative thinking as an unhelpful habitual response and focuses on the use of functional analysis of rumination. Thus, RFCBT combines behavioral activation strategies with novel techniques to foster a concrete, process-focused style of thinking. In support of this model, an RCT comparing treatment-as-usual (TAU, including antidepressant medication) versus TAU plus RFCBT in patients with medication-refractory residual depression found that the addition of RFCBT reduced depressive symptoms more than medication alone [65]. RFCBT was found to improve remission rates (62% vs. 21%) and reduce relapse rates (10% vs. 53%) at 6 months post-treatment, with changes in rumination scores found to be a significant mediator of these effects. A further independent trial found that RFCBT improved depressive symptoms and reduced rumination, relative to a waiting list control group, in patients with residual depression [66]. More recently, RFCBT has been evaluated in adolescents and young people and as a preventive treatment for youth at increased risk for depression with promising results. In a high-risk preventive design, group and internet RFCBT were compared to a waiting list control condition in a large sample of Dutch adolescents and young adults with elevated rumination, but without current depression. Relative to the waiting list control, both RFCBT interventions significantly reduced rumination and depression at post-intervention and one-year follow-up, and halved the one-year incidence rates of depression [67]. In another preventive study, guided online RFCBT significantly reduced the subsequent onset of major depression, relative to a usual practice control, in UK undergraduates with elevated rumination, especially for those young people reporting higher levels of stress at baseline [68].

Importantly, a recent pilot RCT compared 8 weeks of TAU+RFCBT to TAU+assessment in 33 adolescents with a history of major depression who were at risk of relapse and observed that RFCBT significantly reduced rumination and depression relative to the TAU control group [69]. fMRI scans pre- and post-intervention showed that adolescents who received RFCBT demonstrated significant decreases in rs-fMRI connectivity between regions of DMN (the left posterior cingulate cortex) and the CCN (the right inferior frontal gyrus and bilateral inferior temporal gyri). The degree of change in connectivity was correlated with changes in self-reported depression and rumination, suggesting that the DMN and CCN may begin to function more independently (or in less conflict) as rumination reduces. RFCBT therefore is a promising candidate intervention for the prevention of depressive relapse and recurrence in adolescents following prior depressive episode(s), and may improve longer term outcomes for this at-risk population.

These findings indicate that RFCBT is able to modify rumination in adolescents, and shows potential as a targeted intervention to reduce risk of depressive relapse in high-risk adolescents. However, no full-scale study has evaluated RFCBT adapted for adolescents at risk of depressive relapse. Moreover, research has not yet revealed the neural mechanisms underlying increases or decreases in rumination, either in the moment or over time. This knowledge regarding the neural processes affecting rumination is particularly pertinent during the critical developmental period of adolescence, when ruminative habits typically emerge.

## Aims and objectives

The primary aim of this phase III, two-stage prevention mechanism randomised controlled trial is to evaluate whether RFCBT is effective in reducing the primary outcomes of (a) self-reported rumination and (b) rs-fMRI connectivity between regions of the DMN and CCN, when compared to a TAU + assessment-only (AO) control arm in the first stage (NIMH R61 grant phase) (assessments performed within context of the study and TAU provided in community), assessed at primary endpoint of 16-20 weeks post-baseline. These indices are chosen as potential predictors of risk for future depression; that is, this operates as a targeted trial of a prevention mechanism [30, 70]. The second stage (potential NIMH R33 grant phase if Go targets are met in first stage) includes comparison of RFCBT to relaxation therapy on the same primary outcomes. Secondary outcomes include change in symptoms of depression at 16 weeks, recurrence of depression over 12 months post-intervention period, and whether engagement with therapy homework (as a dose measure) is related to changes in the primary outcomes.

## Methods

### Study design

The study consists of a two-arm parallel-group single-blind randomised controlled trial. Stage 1 compares RFCBT to TAU + AO; stage 2 compares RFCBT to TAU + relaxation. The assessment team members will be blind to treatment arm. Our primary hypotheses are that RFCBT will be superior to the control arm in reducing (a) rumination, and (b) rs-fMRI connectivity between DMN and CCN. Our secondary hypotheses are that (a) that RFCBT will be superior to the control arm in reducing recurrence of depression over 12 months; and (b) engagement with RFCBT homework (dose response) will be related to changes in (i) rumination, (ii) DMN and CCN resting state connectivity, and (iii) degree of change in regional brain activation during a rumination induction from pre- to post- treatment. The study design was published in the National Clinical Trials Website (NCT03859297) in March 2019. The only substantive change is the move to tele-assessment and teletherapy in March 2020 in response to the COVID-19 pandemic. The neuroimaging protocol was discontinued from March through June 2020, and then reinstated with COVID-19 safety precautions.

### Study setting

The study takes place at the University of Utah in the United States of America. Participants attend assessment appointments at the Huntsman Mental Health Institute (formerly University Neuropsychiatric Institute) on the University of Utah campus, which provides primary inpatient and outpatient psychiatric services to young people and adults who are primarily residents throughout the Salt Lake Valley and Intermountain West region.

### Eligibility criteria

Eligible participants will be postpubertal adolescents aged 14-17 with a previous diagnosis of Major Depressive Disorder (MDD), based on the Diagnostic and Statistical Manual (DSM-5) [71] criteria and confirmed by assessments using the Kiddie Schedule for Affective Disorders and Schizophrenia – Present and Lifetime Version DSM-5 (KSADS-PL) [72, 73] (*N* = 60 in stage 1 and *N* = 120 in stage 2). Participants must have been in full or partial remission for a minimum of 2 weeks (typically much longer); partial remission is defined as meeting less than five clinical-threshold symptoms for MDD according to the KSADS-PL. In addition, participants will be required to have elevated levels of rumination, defined as an elevated Rumination Response Scale (RRS) [35]. Age-adjusted RRS threshold cut-offs for males are from 28 to 31 and for females from 35 to 38; the minimum cut-off levels increase with participant age [35, 74].

Exclusion criteria include a lifetime history of conduct disorder, autism spectrum disorder, any psychotic disorder (or psychotic episode unexplained by other known medical causes), or bipolar disorder, an estimated intelligence quotient (IQ) of 75 or less as estimated by a computer adaptation of the Synonym Knowledge subtest [75]; elevated current depressive symptoms as indicated by a raw score greater than 45 on the Children’s Depression Rating Scale – Revised (CDRS-R) [76]; endorsing suicide attempt or plan within the past 6 months, as assessed by the KSADS-PL, CDRS-R, and Lifetime Suicide Attempt Self-Injury Interview (L-SASI) [77]; reporting anorexia/bulimia or alcohol/substance abuse within the past 6 months. Currently receiving psychotropic medication other than stimulants for ADHD and antidepressants (e.g., anxiolytics and most atypical antipsychotics) will be exclusionary with the exception of those that are prescribed for treating depression only. If taking medications, participants will be required to have been on a stable dose of medication for the past 4 weeks, with no change in specific medication for past 6 weeks. The study will also exclude individuals reporting current or recent (past year) treatment with CBT, or related variants (e.g., detailed-oriented structured therapy involving elements such as cognitive restructuring, homework, or a CBT focus), and those reporting prior treatment with rumination focus. Due to residual concerns from institutional review boards about the brain imaging protocol, individuals who are currently pregnant are excluded. For safety and data quality reasons, those who have MRI contraindications including non-removable metal braces, tattoos with metal, or claustrophobia are excluded. In instances where potential participants either decline consent or provide consent but do not meet eligibility requirements, we will offer a list of clinically relevant treatment resources outside of the study, including the option of receiving the same treatment in outpatient clinic from one of the investigators. We will keep information collected from participants who consented and were later deemed ineligible for the purposes of assessing generalizability and sample representativeness.

### Recruitment

Participants for the proposed study will be recruited from the University of Utah Hospitals and Clinics and from a number of additional sources and organisations (e.g., The Balanced Mind Foundation, National Alliance on Mental Illness, American Foundation for Suicide Prevention), via advertisements on local radio stations (e.g., KSL radio), in schools, on social media (e.g. Facebook, NextDoor), and on Utah public transit (between May 2019 and May 2021 (estimated)). Adolescent/young adult-based hospitals and clinics, as well as high schools and universities in the Salt Lake City area, will be locations targeted for additional recruitment. Our successful retention rates with pilot work (approximately 83% over 2 years [69]) will be bolstered through close contact with all study participants and close monitoring at weekly research team meetings. If obstacles to study recruitment and retention are encountered, contingency plans such as increased advertisement, increased resources to cover research assistant time focused on recruitment outreach efforts, announcements to colleagues, and scheduled calls to participants, will be developed to address these challenges in collaboration with the team. Following verification of initial eligibility via telephone screening, participants are scheduled for a baseline visit during which we obtain complete written informed parental consent and adolescent participant assent prior to enrolment in the study. Parents will also be asked to consent to contribute information about the adolescent and relevant family medical history. For adolescents who turn 18-years-old during the course of the study, they will be asked to provide written informed consent to continue in the study once they are aged 18. Further eligibility will be determined by the research team via administration of the KSADS-PL, CDRS-R, RRS, and Synonyms Knowledge Test at the baseline visit. After the final baseline assessment procedures (diagnostic, neuropsychological, fMRI, and the stress and relaxation session), the patients will be randomly assigned to receive RFCBT or participate in the control group.

### Participant timeline

For further details on participant timeline, see Figs. 1 and 2.

**Fig. 1 Fig1:**
[figure not shown]
RuMeChange schedule of enrolment, interventions, and assessments

**Fig. 2 Fig2:**
[figure not shown]
CONSORT flow diagram for RuMeChange

### Sample size

This trial was funded as the first stage (R61 grant) in a potential two-stage study, with the second stage (R33 grant) comparing RFCBT to an active control of relaxation therapy. Moving to the second stage is contingent on the first stage meeting the Go criteria of baseline to post-intervention between-treatment arm effect size changes of .5SD (effect size) in RRS and .5SD (effect size) in rs-fMRI connectivity from left PCC to right IFG. These effect sizes were chosen to reflect a noticeable clinical difference, necessary to progress to second stage. For this stage, the target recruitment is *n* = 30 per group. Power was computed using gPower 3.1 for a repeated measurements model in the first stage (R61), to compare the effects of RFCBT versus TAU + AO where observations are nested within subjects, targeting a .5SD (effect) size change, and with known reliability of RRS (*r* = .77) and rs-fMRI connectivity of left PCC to right IFG (*r* = .71). On this basis, a target recruitment of *n* = 30 per treatment arm is estimated to provide power of .99 for RRS and .98 for rs-fMRI. Assuming up to 15% follow-up attrition at post-intervention follow-up, power remains >.94 for both comparisons. For the R33 stage, there will be an active treatment comparator so the effect size difference is likely to be smaller. To achieve adequate power to detect a meaningful clinical difference, we assumed a minimum difference of 0.22 SD for each comparison; for power at 0.80, alpha at 0.05, assuming 15% follow-up attrition, we need to recruit 60 young people per treatment arm (*N* = 120).

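### Stage 2 sample size: 60 per arm with 15% attrition does not give .80 power for a 0.22 SD between-arm difference in each primary outcome

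*Protocol article*

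**What the plan says.** All the sizing statements are in the protocol article, Sample size. For the R33 stage the authors expect a smaller effect because the comparator is active. They write "we assumed a minimum difference of 0.22 SD for each comparison; for power at 0.80, alpha at 0.05, assuming 15% follow-up attrition", and conclude that "we need to recruit 60 young people per treatment arm", 120 in total.

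The only correlations in the document are in the same section, for Stage 1: .77 for RRS and .71 for left PCC to right IFG connectivity. They are labelled reliability and enter a G*Power 3.1 repeated-measures calculation. Nothing is restated for Stage 2 on correlation, sidedness, the SD to which 0.22 refers, or the software settings.

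Three other sections bear on the check. Statistical methods makes the group-by-time interaction the treatment test. Primary outcome fixes two MRI scans per participant, at baseline and post-intervention. Randomisation and allocation concealment adds bi-weekly RRS reports between baseline and post-treatment.

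**The concern.** A difference of 0.22 SD is small, and about 50 evaluable participants per arm is a small sample in which to find it. Correlation between baseline and follow-up helps, but at .77 and .71 it does not help nearly enough.

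Stage 2 is the comparison that controls for therapist contact, structure and attention, so it bears on whether RFCBT has a rumination-specific effect. The protocol presents 0.22 SD as the minimum difference assumed in order to detect a clinically meaningful one. On a baseline-to-post analysis, a true effect of that size would be missed roughly 60-70% of the time, against the 20% that the text implies. A null result could then be misread as evidence of no specific benefit.

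**Working it through.** **Inputs.** Difference 0.22 SD, alpha .05, target power .80, attrition 15% and 60 per arm, all from Sample size. Evaluable per arm: 60 × 0.85 = 51, or 102 in total. Correlations r = .77 (RRS) and .71 (rs-fMRI), from the Stage 1 text. Two-sided testing is my assumption. Result pairs below are RRS / rs-fMRI.

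**1. Difference in change (the group-by-time test with two time points).** In units of the outcome SD, the SD of change is √(2(1 − r)).
- r = .77: √0.46 = .678, standardised difference .22/.678 = .324
- r = .71: √0.58 = .762, standardised difference .22/.762 = .289

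The noncentrality is d√(n/2) = d√25.5, giving 1.64 / 1.46 on 100 degrees of freedom. Two-sided power is **.37 / .30**, against the stated .80.

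**2. Baseline-adjusted analysis.** The residual SD is √(1 − r²) = .638 / .704. The standardised difference is .345 / .312 and the noncentrality 1.74 / 1.58. Power is **.41 / .35**.

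**3. More generous readings.**

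| Reading | RRS | rs-fMRI |
|---|---|---|
| Change score, no attrition (60 per arm) | .42 | .35 |
| Change score, one-sided, 51 per arm | .49 | .42 |
| Baseline-adjusted, one-sided, 51 per arm | .53 | .47 |
| Baseline-adjusted, one-sided, no attrition | .59 | .52 |

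Reading 0.22 as a fraction of the change-score SD makes matters worse, with power .20. To reach .80 two-sided with 51 per arm, the pre-post correlation would have to be about .92.

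**4. Bi-weekly RRS reports.** Over 16-20 weeks these give about 8-10 measurements. An idealised omnibus interaction test with equal correlations of .77 and N = 102 gives .65 with 8 measures and .72 with 10. With 10 measures and no attrition it reaches .80. This does not apply to rs-fMRI, which has two measurements.

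**5. What 51 per arm can detect at .80 (two-sided).** Change score: **0.38 / 0.43 SD**. Baseline-adjusted: **0.36 / 0.39 SD**. For reference, 0.22 SD at .80 would need 151 / 190 completers per arm on change scores, or 134 / 162 with baseline adjustment.

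**6. Looking for the source of the stated .80.** In the G*Power interaction test with two measures, the noncentrality is λ = f² × N × 2/(1 − r). In a 2 × 2 layout, a between-arm difference in change of δ SD corresponds to f = δ/4.
- f = .22/4 = .055, N = 102: λ = 2.68 / 2.13, power .37 / .30, agreeing with step 1.
- f = .22/2 = .11, N = 102: λ = 10.73 / 8.51, power .90 / .82. This f corresponds to 4 × .11 = 0.44 SD.
- A one-sided paired t test within one arm, n = 60, r = .77, 0.22 SD: power .80. It ignores both attrition and the control arm.

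The Stage 1 figures do not settle which was used. For .5 SD and 30 per arm the protocol states .99 / .98. The two-arm difference in change gives .80 / .71. Entering f = .5/2 = .25 gives 1.00 / .999. A one-sided within-arm paired test gives .99 / .97.

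**The case against.** **The inputs are not fully fixed.** The correlations are called reliability and belong to Stage 1; sidedness and the reference SD are unstated. This stands, and it is why the figures above are conditional. It does not rescue the claim: the most favourable two-measurement reading gives .59 / .52, and a correlation of about .92 is far from the only values printed.

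**The RRS analysis may use more than two time points.** Statistical methods specifies a longitudinal mixed model and multiple imputation with auxiliary variables. This also stands. The .37 for RRS is a two-time-point figure, and 51 per arm is an approximation. A reader might infer that RRS power is .37 under whatever model is fitted; the documents do not support that. Equally, the idealised 8-10 measure model stays below .80 after attrition, and the protocol claims .80 for each comparison, including rs-fMRI.

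**The cause.** It is tempting to conclude that 0.22 was halved rather than quartered when converted to f, so that the plan is out by a factor of two. The documents do not support this as a finding. The Stage 2 settings are not stated, f = .11 gives .90 / .82 rather than .80, another route also gives .80 for RRS, and the same halving does not reproduce the Stage 1 figures. It is one possible explanation.

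**Stage 2 is only potential.** It depends on the Stage 1 Go criteria. That leaves time to correct the statement but does not make it right.

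**Conclusion.** The concern holds. As printed, the Stage 2 effect size, power, alpha, attrition and sample size cannot all be true for both primary outcomes. On a two-time-point analysis, power at 0.22 SD is about .30-.41 instead of .80, and the differences detectable at .80 are about 1.6 to 1.9 times the stated one (0.36/0.22 to 0.43/0.22). The result is firmest for rs-fMRI, where the number of scans is fixed at two; for RRS it depends on how the bi-weekly reports are used.

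This rests on a two-sided test, 51 evaluable per arm, 0.22 expressed in SDs of the outcome, and the Stage 1 correlations applying as pre-post correlations in Stage 2. It does not rest on any account of how the figure arose. It is a wrong statement in the article, not detail left to a fuller document, and should be corrected before Stage 2 relies on it.

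**What to change.** Keep N = 120 and restate what it provides: with 60 per arm and 15% attrition, .80 power for about 0.38 SD (RRS) and 0.43 SD (rs-fMRI) on change scores, or 0.36 and 0.39 SD with baseline adjustment; power at 0.22 SD is about .30-.41 on a two-time-point analysis. Remove the claim that 0.22 SD is detectable at .80 for each comparison. State the effect-size definition (which SD, and difference in change or adjusted post score), the correlation, the sidedness and the software settings. If the bi-weekly RRS reports are to be counted towards RRS power, give that calculation separately with its assumed number of measures and correlation structure.

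The cost is a few reworded sentences and a less favourable figure, with no added participants. The restatement makes the power claim accurate; it does not make 0.22 SD detectable. If the investigators need .80 at that difference on change scores, the size would be about 151/0.85 ≈ 178 (RRS) or 190/0.85 ≈ 224 (rs-fMRI) recruited per arm.
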